### Participants and recruitment

The patients will be recruited from rheumatology clinics under consultant’s advice. Self-referred patients will be involved through advertisements on noticeboards or websites/newspapers. All the questionnaires, indexes and scores mention in this section are detailed in the Additional file 1.

Any male or female patients older than 18 that fulfil the CASPAR or the BASDAI criteria will be invited for screening. They will receive the full patient information sheet (PIS) and informed consent forms (ICF). Potential participants will be allowed to consider full implications of taking part in the study for a minimum of 24 h before screening. They will also have the opportunity to ask questions before signing the consent.

Patients will not be able to take part to the study if they:
Are not able to give informed consentAre pregnant or breastfeedingHave a history of alcohol, drugs or chemical abuse in the 3 months prior to screeningHave recently changed their diet (less than 4 weeks)Have not been on a stable therapy with DMARDs in the 3 months prior to enrolmentExperienced any gastrointestinal symptom (diarrhoea, vomiting, abdominal pain, constipation) in the 4 weeks prior enrolmentTaken antibiotics in the 3 months prior to enrolmentHave been diagnosed with cancer in the past 3 years or any primary or secondary immunodeficiencyHave had endoscopy procedures carried out in the 8 weeks prior to enrolment or any gastro-intestinal surgery in the last 6 monthsMake regular use of laxatives and/or agents that affect gut motility

The healthy volunteers will be approached by the healthy volunteer data manager at Imperial College London and will also able to self-refer through advertisements. After consenting there will be a questionnaire. The volunteer will be asked to complete a self-description of health. This will be evaluated by one of the investigators, and any healthy volunteer with no current medical conditions and not in use of prescribed or self-prescribed medication (except for multivitamins) will be enrolled in the study.

All the participants to the study will receive a physical examination with assessment of vital signs (pulse and blood pressure), weight, height and body mass index (BMI). The medical and medication history will be reviewed with collection of data on demographics, diet and lifestyle. All concomitant medications will be recorded, including probiotics or fermented milk products.

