#### Trial challenge

Emerging evidence has been linking the microbiome with several diseases including autoimmune diseases such as Psoriatic Arthritis [14]. In a paper published in 2015 [21], Scher and colleagues described the observation of a less diverse microbiome in 16 subjects affected by Psoriatic arthritis. Comparing samples taken from patients with psoriatic arthritis, psoriasis and healthy volunteers they observed a lower abundance of specific beneficial taxa of the gut microbiome in the first two groups. Furthermore, the patients with psoriatic arthritis showed other immunologic alterations with increase in fecal sIgA levels, decrease of RANKL and Osteoprogerin (which may affect the antigen presentation process in the gut) and decreased quantities of medium chain fatty acids (MCFAs). From studies conducted on healthy volunteers we know that the microbiome is constantly reshaping under the influence of individual and environmental factors [27–29]. Among the environmental factors, the diet [30, 31] exerts an extremely important role. It has been documented that a change of diet is actually able to modify the microbiome in as little as one or 2 days [32]. In order to detail accurately the relationship between food intake and microbiome, Johnson and colleagues [33] conducted a small clinical trial study on 34 healthy volunteers who were randomised to introduce with different diets. The results of the trial show the potential role of different food and micronutrients in influencing different bacteria strains in a population of healthy volunteers.

The hypothesis of our study was that the microbiome-metabolic interface of psoriatic arthritis patient is distinct comparing to healthy volunteers. The food diary included in the study enlists different elements in the 5 food groups and the possible effect of portion size is taken into account using visual aids to help the patients to describe in the most accurate way the amount of food they have introduced with any meal. The time of the different meals is taken into consideration as are soft and alcoholic drinks.

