#### Sample size consideration

Estimate adequate sample sizes is complicated due to the lack of consensus in microbiome studies. Classical power calculations, used for clinical trials, are not a robust manner to assess the numbers of individuals required for exploratory and observational microbiome studies [34] since the SD and means of the sample populations is not known.

The recruitment strategy will be based on previous studies in inflammatory arthropaties [15, 21]. The variance in Th17, Treg numbers, IL-17 and IL − 22 cytokine measurements was estimated on the basis of previous clinical trials results [24]. Assuming a 2-sided significance level of 5% (a = 0.05) and a power 1-b of 95% (level at which we set the null hypothesis) and a 25% difference in IL − 17A secretion between controls and PsA, we needed to recruit a minimum of 24 study participants into each group (healthy volunteer, PsA and AS). Due to the nature of the sampling and the multiple visits to the clinic, we have set the target in 30 volunteers or more per group, to allow for dropout rate of 10% and to ensure robustness. First approach to subject lost to follow-up would be replaced to maximise data outcome and study objectives, otherwise the subject would be included with the acquired data.

In conclusion the study target to enrol 65 eligible patients with psoriatic arthritis (45 at the Bath centre and 20 at the London centre), 30 with ankylosing spondylitis, and 30 healthy volunteers.

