### Analysis plan and data management

The phenomic characterisation will take place during the later stage of the study (Table 2) and it involves 3 different arms of analysis: microbiome, immunology and metabonome analysis.

Bacterial DNA will be extracted from faecal samples, to define bacterial diversity and taxonomy. Whole genome sequencing, 16S rRNA gene sequencing and Nanopore sequencing will provide a taxonomic analysis and taxon list in PsA, AS and healthy individuals. Furthermore, this procedure will provide a comparative between the different sequencing technologies and its possibilities in clinical studies.

The immunological analysis will measure proportions of Th17and Treg subsets in peripheral blood samples using multi-parametric flow cytometry. T cells subsets will be use to look for associations between composition of gut microbiome and proportion of circulating Th17 and Treg in study participants. Serum samples will also be used for analysis of pro-inflammatory cytokines (IL-1β, IL-6, and IL-23p19).

NMR and UPLC-MS measurements of all urine, blood and faecal samples for metabolite profiling will be used for the metabonomic characterization. This metabonomic dataset will be used for biomarker ID and functional metabolic discriminators of PsA.

Finally, gut microbiome sequencing datasets will be integrated with biofluid metabolite profiles to identify important biological pathways in specific individuals. In the first stage we will correlate the metabolic profiles from NMR based metabonomics with the pattern of the abundance of microbial taxonomic entities and in a second phase evaluating enrichment of specific ontologies or metabolic functions from metagenomic databases. Once key pathways are statistically pinpointed, we will look into metabolic fluxes as integrated by different taxonomic entities.

The aim is to link gene composition, host metabotypes and immunotypes. We will use the whole gut microbiota community to pinpoint which functions are enriched/depleted in PsA cohorts and whether there are functions which correlate with disease or act as biomarkers of disease.

Meta-gene analysis (i.e. targeted functional metagenomics) will be used to establish the bile salt hydrolases, SCFA synthesizing genes and glucuronidases in gut samples. This approach will link specific functional gene diversity with specific metabotypes.

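### Read together, the eligibility sentences keep probiotic users out of the control group but admit them as PsA or AS patients, so ingested strains could contribute to a disease-versus-healthy taxon difference

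*Protocol article*

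**What the plan says.** Three statements in Participants and recruitment bear on this.

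- On recording: "All concomitant medications will be recorded, including probiotics or fermented milk products". The sentence closes a paragraph that applies to every participant.
- On controls: a volunteer must have no current medical condition and be "not in use of prescribed or self-prescribed medication (except for multivitamins) will be enrolled in the study". Multivitamins are the only exception given.
- On patients: the exclusion list covers antibiotics within 3 months, a diet change less than 4 weeks old, and regular use of laxatives or motility agents. Probiotics are not on it.

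The affected comparison is the study hypothesis in Trial challenge, that the "microbiome-metabolic interface of psoriatic arthritis patient is distinct comparing to healthy volunteers". The affected output is in Analysis plan and data management, where faecal sequencing "will provide a taxonomic analysis and taxon list in PsA, AS and healthy individuals". The Abstract and the Discussion say that diet is assessed in all participants over 7 days.

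**The concern.** A probiotic delivers live bacteria into the stool that is then sequenced. If its use is possible in patients and ruled out in controls, a product strain can appear in the PsA or AS taxon list and be absent from the healthy list with no disease effect behind it. The planned shotgun sequencing is meant to identify species, so such organisms could be picked out individually.

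The Discussion says that controls will be matched to the PsA cohort to limit environmental differences and that recruitment was designed to limit confounding. An eligibility rule that links a microbial exposure to group works against both aims. Antirheumatic drugs differ between patients and controls because of the disease; probiotic use need not, so a common rule is feasible.

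**Working it through.** **Step 1: what the text implies for each group.**

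| | Healthy volunteers | PsA and AS patients |
|---|---|---|
| Class of probiotics | concomitant medication | concomitant medication |
| Medication rule | none except multivitamins | no general bar; named exclusions only |
| Probiotics among named exclusions | covered by the medication rule, by inference | no |
| Result for a stable user | not eligible | eligible, use recorded |

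PsA and AS follow the same rule, so the asymmetry lies between each disease group and the controls.

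**Step 2: inputs for an illustration of size.** The article gives no figure on this point to reproduce. Its sample size rests on IL-17A and does not bear on it. Group sizes are 65 PsA, "30 with ankylosing spondylitis, and 30 healthy volunteers". The two-sided 5% level is borrowed from Sample size consideration. *Assumptions:* 10% to 20% of PsA patients carry one and the same product strain, and no control carries it from any source.

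**Step 3: PsA versus healthy, Fisher's exact test.** With k carriers in total, the probability that all fall among the 65 patients is C(65,k)/C(95,k). The two-sided p-value adds the other tables that are no more probable.

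| Carriage in PsA | k of 65 | C(65,k)/C(95,k) | Two-sided p against 0 of 30 |
|---|---|---|---|
| 10% (6.5) | 7 | 0.063 | 0.094 |
| 15% (9.75) | 10 | 0.018 | 0.028 |
| 20% (13) | 13 | 0.005 | 0.008 |

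The smallest count that gives p < 0.05 is 10 of 65. For AS against controls it is 6 of 30 (p = 0.024).

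**Step 4: chance of a nominally significant strain with no disease effect.** For PsA this is P(X ≥ 10) with X ~ Bin(65, u). For AS it is P(X ≥ 6) with X ~ Bin(30, u). Controls are held at zero.

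| Carriage u in patients | PsA v healthy | AS v healthy |
|---|---|---|
| 5% | 0.1% | 0.3% |
| 10% | 11% | 7% |
| 15% | 52% | 29% |
| 20% | 86% | 57% |
| 30% | 99.8% | 92% |

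If controls carried the strain at the same rate as PsA patients, the PsA figures at 10%, 15% and 20% would be 2.7%, 3.4% and 3.7%. The excess therefore comes from the unequal rule.

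**Step 5: how fragile the illustration is.**

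- *Several products.* If the 13 carriers split 7 and 6 over two strains, the p-values are 0.094 and 0.172, and neither reaches 5%.
- *Multiplicity.* Under Bonferroni, p = 0.0079 passes only up to 0.05/0.0079 = 6.3, that is, 6 tests. A community-wide screen would involve many more.

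**Step 6: what the recorded data can repair.** At 10% to 20% use, 65 − 7 = 58 to 65 − 13 = 52 PsA patients are non-users. Comparing them with the 30 controls removes this exposure, at the cost of 7 to 13 patients.

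**The case against.** **The bar in controls is not written down.** No sentence says that a volunteer may not take a probiotic. The recording sentence covers all participants and may simply widen what is recorded. Taken strictly as a definition, it would also reject any volunteer who consumes fermented milk, which seems unlikely to be intended. This stands: the bar is an inference from two sentences. But on the looser reading those sentences pull against each other and sites could screen controls differently, so the text needs settling either way.

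**The article is condensed.** The Abstract applies to volunteers some exclusions that the body lists only for patients, so the volunteer criteria may be fuller than shown. This is a fair caution against arguing from silence. The control medication rule and its single exception are, however, stated outright.

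**Much is already captured.** The diary covers everyone, and the 4-week diet exclusion may catch a patient who has newly started fermented milk. Both points stand. Neither clearly covers a supplement, and the exclusion leaves stable use untouched.

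**Adjustment is possible.** A reader might infer that probiotic use cannot be separated from group. The documents do not support that. Under an additive model the effect of use can be estimated among the 95 patients, and non-users against controls gives the group effect. What remains is that, with no exposed controls, the additive assumption cannot be checked in them. An analysis plan not shown may cover the handling; the point here is the eligibility rule, not a missing model term.

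**The size is unsourced.** This stands too; see steps 2 and 5 of the working.

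**Conclusion.** The point holds as an inferred asymmetry. On the plain reading of Participants and recruitment, probiotic users are kept out of the control group and admitted to the patient groups, so product strains could contribute to a PsA-versus-healthy or AS-versus-healthy taxon difference. PsA versus AS is largely unaffected.

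The size is unknown because no usage rate is given. The p-values of about 0.09 to 0.008 for PsA assume 10% to 20% carriage of one shared strain, none in controls and no multiplicity correction; relaxing any of these weakens the signal. A reader might go further and conclude that controls have zero users by explicit rule, or that a false PsA signature is to be expected. The documents support neither: the first is an inference and the second depends on figures they do not contain. The matter is still worth correcting, because the remedy is cheap and acts on the comparison that the study is built around.

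**What to change.** 1. State one eligibility rule on probiotic supplements that applies equally to all four cohorts before each stool sample, including the repeat visits of Group A. The investigators should choose the rule and any window; what matters is that it is the same for everyone.
2. Treat fermented milk products as diet, using the 7-day diary that all participants already complete, and say that they are not an excluded medication for healthy volunteers.
3. Repeat the PsA-versus-healthy and AS-versus-healthy taxonomic comparisons without recorded probiotic users. This also serves participants already enrolled.

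The cost is an eligibility sentence, a clarification on fermented milk and one sensitivity analysis on data already collected. A few patients may be delayed or left out of the sensitivity set.

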### Withdrawal criteria

Study participants will be informed that they have the right to withdraw from the study at any time for any reason, without prejudice to their medical care. The investigator can withdraw subjects from the study for any of the following grounds:
Subject request.Subject is lost to follow-up (LTFU).Development of an intercurrent illness, condition, or procedural complication, which would interfere with the subject’s continued participation.The investigator also reserves the right to withdraw subjects in the interest of subject safety and welfare.

### Adverse events

#### Definition

##### Adverse Event (AE)

Any untoward medical occurrence in a patient or clinical study subject [24]. This includes occurrences that are not necessarily caused by or related to a medicinal product administered. An adverse event can, therefore, be any unfavourable and unintended signs [25], abnormal laboratory values, and symptoms or disease temporarily associated with or not associated with study activities.

##### Serious Adverse Event (SAE)

Serious Adverse Event. An untoward occurrence that: (a) results in death; (b) is life-threatening; (c) requires hospitalisation or prolongation of existing hospitalisation; (d) results in persistent or significant disability or incapacity; (e) consists of a congenital anomaly or birth defect.

Medical judgement should be exercised in deciding whether an AE is serious in other situations. Important AEs that are not immediately life-threatening or do not result in death or hospitalisation but may jeopardise the subject or may require intervention to prevent one of the other outcomes listed in the definition above, should also be considered serious [26].

#### Reporting procedures

All adverse events should be reported. Depending on the nature of the event the reporting procedures below should be followed. Any questions concerning adverse event reporting should be directed to the Chief Investigator in the first instance.

All such events, whether expected or not, should be recorded. This starts from the signed informed consent for participation in the trial until the last visit.

Adverse events should be documented in the participant’s source document sheet.

Adverse events to be graded according to the degree of severity as follows:
Grade 1 - Mild, usually transient in nature and does not interfere with normal activity, observation only, no intervention, is needed.Grade 2 - Moderate, interfere with normal activities minimal, local or non-invasive intervention indicated; limiting age-appropriate.Grade 3 - Severe or medically significant but not immediately life-threatening; hospitalisation or prolongation of hospitalisation indicated; disabling; limiting self-care ADL.Grade 4 - Life-threatening consequences; urgent intervention indicated.Grade 5 - Death related to AE.

Abnormal laboratory tests results constitute adverse events only if they:
Induce clinical signs and symptomsThey are considered clinically significant by the investigatorThey require intervention

Clinically significant abnormal laboratory test results should be identified through a review of Lab values outside normal ranges as per hospital policy and procedures. Notable or significant changes from the baseline or previous visit values, which are considered to be clinically significant, to be documented in the medical notes and reported to their general practitioner and Serious AEs.

An SAE form should be completed and given/sent to the Chief Investigator within 24 h. However, relapse and death due to PsA or AS and hospitalisations for elective treatment of a pre-existing condition do not need reporting as SAEs. All SAEs should be reported to the approving REC where in the opinion of the Chief Investigator, the event was:
‘related’,i.e. resulted from the administration of any of the research procedures; and‘Unexpected’, i.e. an event that is not an expected occurrence of the study procedures.

Reports of related and unexpected SAEs should be submitted within 15 days of the Chief Investigator becoming aware of the event, using the NRES SAE form for non-IMP studies. The Chief Investigator must also notify the Sponsor of all SAEs.

Local investigators should report any SAEs as required by their Local Research Ethics Committee, Sponsor and/or Research & Development Office.

#### Trial challenge

Emerging evidence has been linking the microbiome with several diseases including autoimmune diseases such as Psoriatic Arthritis [14]. In a paper published in 2015 [21], Scher and colleagues described the observation of a less diverse microbiome in 16 subjects affected by Psoriatic arthritis. Comparing samples taken from patients with psoriatic arthritis, psoriasis and healthy volunteers they observed a lower abundance of specific beneficial taxa of the gut microbiome in the first two groups. Furthermore, the patients with psoriatic arthritis showed other immunologic alterations with increase in fecal sIgA levels, decrease of RANKL and Osteoprogerin (which may affect the antigen presentation process in the gut) and decreased quantities of medium chain fatty acids (MCFAs). From studies conducted on healthy volunteers we know that the microbiome is constantly reshaping under the influence of individual and environmental factors [27–29]. Among the environmental factors, the diet [30, 31] exerts an extremely important role. It has been documented that a change of diet is actually able to modify the microbiome in as little as one or 2 days [32]. In order to detail accurately the relationship between food intake and microbiome, Johnson and colleagues [33] conducted a small clinical trial study on 34 healthy volunteers who were randomised to introduce with different diets. The results of the trial show the potential role of different food and micronutrients in influencing different bacteria strains in a population of healthy volunteers.

The hypothesis of our study was that the microbiome-metabolic interface of psoriatic arthritis patient is distinct comparing to healthy volunteers. The food diary included in the study enlists different elements in the 5 food groups and the possible effect of portion size is taken into account using visual aids to help the patients to describe in the most accurate way the amount of food they have introduced with any meal. The time of the different meals is taken into consideration as are soft and alcoholic drinks.

#### Sample size consideration

Estimate adequate sample sizes is complicated due to the lack of consensus in microbiome studies. Classical power calculations, used for clinical trials, are not a robust manner to assess the numbers of individuals required for exploratory and observational microbiome studies [34] since the SD and means of the sample populations is not known.

The recruitment strategy will be based on previous studies in inflammatory arthropaties [15, 21]. The variance in Th17, Treg numbers, IL-17 and IL − 22 cytokine measurements was estimated on the basis of previous clinical trials results [24]. Assuming a 2-sided significance level of 5% (a = 0.05) and a power 1-b of 95% (level at which we set the null hypothesis) and a 25% difference in IL − 17A secretion between controls and PsA, we needed to recruit a minimum of 24 study participants into each group (healthy volunteer, PsA and AS). Due to the nature of the sampling and the multiple visits to the clinic, we have set the target in 30 volunteers or more per group, to allow for dropout rate of 10% and to ensure robustness. First approach to subject lost to follow-up would be replaced to maximise data outcome and study objectives, otherwise the subject would be included with the acquired data.

In conclusion the study target to enrol 65 eligible patients with psoriatic arthritis (45 at the Bath centre and 20 at the London centre), 30 with ankylosing spondylitis, and 30 healthy volunteers.

